## **Population-based serosurvey to estimate prevalence of SARS-CoV-2 antibodies in India: Fourth survey, June - July 2021**

India is witnessing a second wave of SARS-CoV-2 infections from February 2021, spread across majority of states of India (1). As of May 29, 2021, India had reported around 25 million cases and more than 3,00,000 deaths (2). The first round of national serosurveillance was conducted from May 11, 2020, to June 4, 2020, among adults in randomly-sampled 700 clusters selected from 70 districts of 21 Indian states. The population-weighted seroprevalence after adjusting for test performance was 0.73% (95% CI: 0.34-1.13). The second round of nationwide serosurvey was conducted between 17 August and 22 September 2020 among individuals aged 10 years and above in the same clusters from 70 districts of 21 states (3). The findings indicated an overall seroprevalence of around 7%, with a ten-fold rise in adult prevalence between May and August 2020. It also indicated a substantial transmission in rural areas with the seroprevalence continuing to be higher in urban slum and non-slum areas (4).

ICMR conducted the third population-based serosurvey among individuals aged 10 years and above and health care workers between Dec 18, 2020 and Jan 6, 2021 in the same 700 villages or wards from 70 districts in 21 states selected for the first and second serosurveys. In the third serosurvey, prevalence was estimated based on the presence of both IgG antibodies against SARS-CoV-2 S1 protein of the receptor binding domain (S1-RBD) and nucleocapsid (N) protein of SARS-CoV-2 while in second serosurvey prevalence was based on IgG antibodies nucleocapsid (N) protein of SARS-CoV-2. The weighted and assay characteristic adjusted seroprevalence among general population was 24.1 (95%CI: 23.0% to 25.3%) The survey indicated that three fourth of the population were still susceptible and a higher sero-prevalence of SARS-CoV-2 infection in urban areas compared to the rural areas (5). Apart from the nationwide serosurveys, several cities and states conducted serosurveys. Metropolitan cities like Delhi, Mumbai, Pune, Chennai, Ahmedabad, Hyderabad have reported seroprevalence ranging between 17.6% and 56% at different timepoints (5).

India started COVID-19 vaccination with BBV152 vaccine (Covaxin; Bharat Biotech) and ChAdOx1 nCoV-19 vaccine (COVID-19 Vaccine AstraZeneca) since January 16, 2021 under Emergency Use Authorization for the health care workers. The vaccination strategy was expanded for frontline workers in February 1, 2021 for frontline workers. In Phase 2 individuals above 60 years old and above 45 years old with specified comorbidities

became eligible for vaccination from March 1, 2021 followed by Phase 3 for all above 45 years of age from April 1, 2021. And finally Phase 4 for all above 18 years of age began on May 1, 2021 (6). Around 44 million individuals have received two doses while 160 million have received at least one dose of vaccine as on May 29, 2021 (7).

Population-based sero-epidemiological studies measure the presence of antibodies against SARS-CoV-2 (natural and vaccine induced) in different age groups. Repeated cross sectional serosurveys conducted in the same geographical location provide estimates to monitor trends over a period of and provide information valuable for the public health decision makers to design and revise containment strategies (8). The earlier serosurveys were conducted among individuals aged 10 years and above and seroprevalence among children below 10 years is still unknown. SARS-CoV-2 poses a high occupational risk to healthcare workers who are at the forefront of managing COVID-19 cases in hospital settings. The third serosurvey indicated seroprevalence around 25% among the HCWs. Also, the HCWs were prioritised for COVID-19 vaccination in the first phase of vaccine rollout in India owing to higher risk of exposure to infected persons.

In this context, it is proposed to conduct fourth round of serosurveillance to determine the prevalence of SARS-CoV-2 antibodies in the community and health care workers as per change in epidemiology and public health response to the epidemic in the country.

The objectives of the fourth survey are:

1. Estimate the prevalence of SARS-COV-2 antibodies among (a) children aged 6-17 y and (b) adults in the general population, at the national level
2. Estimate the prevalence of SARS-COV-2 antibodies among healthcare workers at the national level

## **Methods**

### **Design**

Serial cross-sectional survey

### **Study population**

A] General Population

Inclusion criteria: Usual resident, age  $\geq 6$  years, available at the time of the household visit and willing to participate

Exclusion criteria: Age < 6 years; locked household; guest/visitor; not willing to participate

#### B] Health care workers

Inclusion criteria: Doctors, nurses, paramedical/laboratory staff, employed at the district hospital and sub-district (taluk/CHC) levels, available at the time of hospital visit and willing to participate

Exclusion criteria: Administrative and field staff of hospital; not willing to participate

### **Sample size**

#### A] General population

We plan to enrol 28,000 individuals (19,600 individuals in the age group  $\geq 18$  years, 5600 children in the age group of 10-17 years and 2,800 children in the age group of 6-9 years) across the country by allocating a minimum of 400 individuals to each of the 70 districts that were included in the earlier survey. We have divided the overall sample size of 28,000 in the above-mentioned age groups as per age structure of the population (Census 2011).

The sample size assuming a seroprevalence of 30%, with 10% relative precision, for 95% CI and design effect of 2 would be 1792 for children in the 6-9 age group. The required sample size is sufficient to estimate prevalence for each age group. However, in order to have a sufficiently large sample for a national level survey, we will keep the same overall sample size for the fourth serosurvey.

#### B] Health care workers

We will enrol 7,000 health care workers across the country as done in the third survey.

### **Sampling method**

#### A] General population

We will select 10 clusters (villages in rural areas and wards in urban areas) for each of the district by Probability proportional to size sampling. In each of the selected village/ward, we will select four random locations. In each location, the survey team will choose a random start household and visit consecutive households until 7 individuals from age-group  $\geq 18$  years, 2 children in the age group of 10-17 years and 1 child in the

age group of 6-9 years are enrolled. All household members, 6 years and older, will be included. Within each cluster, 40 individuals (28 individuals from  $\geq 18$  years, 8 children in the age group of 10-17 years and 4 children in the age group of 6-9 years) will be included for the survey. Individuals with history of laboratory confirmed SARS-CoV-2 infection by RT-PCR and/or rapid antigen test will not be excluded. SARS-CoV-2 cases in home isolation will not be included in the survey.

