### **Analysis plan**

#### **A] General population**

We will calculate the frequency of characteristics of survey participants. The reported occupations will be categorised into high and low risk considering the potential risk of exposure to known or unknown COVID-19 case.

We will estimate the seroprevalence of SARS-CoV-2 infection along with 95% confidence intervals using appropriate sampling weights and considering the cluster sampling used for the survey. We will define an antibody positive case as an individual whose sera tested positive on either of the two assays. Hence the sero-prevalence estimated will be based on presence of either N antibodies or S1-RBD antibodies. The final prevalence estimates will be calculated after adjusting for the IgG test performance characteristics of both assays.

We will use the survey data analysis module in STATA software (StataCorp LLC, Texas, USA).

We will separately estimate the seroprevalence of infections only among the adults. In order to maintain comparability with the previous surveys, we will randomly select one adult survey participant per household from the survey database.

We will estimate proportion of individuals with COVID-19 vaccination along with 95% CI. We will also estimate the seroprevalence with 95% CI for SARS-CoV-2 infection by age, sex, locality, occupation, symptom status, contact history, RT-PCR testing and confirmation status.

We will estimate the infection-to-case ratio as the number of individuals with SARS-CoV-2 infection (as per IgG detection) compared to the number of RT-PCR reported cases of COVID-19. We will apply the seroprevalence to the total population above 10 years projected for the year 2020 using 2011 census data to estimate the number of infections in the country. The published literature indicates that the IgG antibodies against SARS-CoV-2 infection start appearing by the end of first week, and most cases are IgG positive by the end of the second week (10). We will consider the number of reported COVID-19 cases 15 days and one week before the initiation of serosurvey to estimate the plausible range of the number of infections. We will estimate the range of the infection fatality ratio (IFR) assuming a three-week lag time from infection to death (11,12)

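### The instruction to include every household member aged 6 and over conflicts with the fixed 7/2/1 quota, and no rule says who fills the last places

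*Combined protocol and SAP*

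**What the plan says.** Three consecutive statements under Sampling method, A] General population, bear on this point.

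1. At each location the team is to "choose a random start household and visit consecutive households until 7 individuals from age-group" 18 and over, together with "2 children in the age group of 10-17 years and 1 child in the" 6-9 group, have been enrolled.
2. "All household members, 6 years and older, will be included".
3. Each cluster contributes 40 people: 28 adults, 8 aged 10-17 and 4 aged 6-9.

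The same section gives the other stages: "We will select 10 clusters" per district, and in each "we will select four random locations". Sample size, A] General population, says "We plan to enrol 28,000 individuals", split 19,600/5,600/2,800, and describes 400 per district as a minimum. The Analysis plan will estimate seroprevalence "using appropriate sampling weights" and gives no formula. It also draws one adult per household from the database, for comparability with the previous surveys.

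No section says what to do with further eligible members once their age group is full while another is still open, or when a household has more eligible members than places left.

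**The concern.** A household rarely fills three age quotas at the same moment. A team reaching its seventh adult before finding a child aged 6-9 must go on to further households. There, statement 2 tells it to enrol the adults, while statements 1 and 3 imply that it should not. Teams in different districts could resolve this differently in good faith.

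Two things are at stake. The first is the size of the operation, since each participant means 3 ml of venous blood and two assays. The second is the last stage of selection. If every member is taken, inclusion within a visited household is certain for those present and consenting. If the quota is kept, inclusion depends on age group, household composition and visiting order, and a member is chosen by no stated rule. The weights differ between the two, so the text does not determine them.

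**Working it through.** **Reproducing the planned totals.** Inputs from the Sampling method and Sample size sections: 70 districts, 10 clusters per district, 4 locations per cluster, 7 + 2 + 1 people per location.

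- Cluster: 4 x 10 = 40; by age 4 x 7 = 28, 4 x 2 = 8, 4 x 1 = 4.
- District: 10 x 40 = 400.
- Total: 70 x 10 x 4 x 10 = 28,000.
- By age: 2,800 locations x 7 = 19,600; x 2 = 5,600; x 1 = 2,800.

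Every stated figure is reproduced, so the planned totals are the quota rule with no overshoot.

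**What happens if every member is enrolled.** The documents do not describe households, so this step is illustrative. Assume that the number of adults in a household is 1 + Poisson and that the numbers aged 10-17 and 6-9 are Poisson. Visit households in turn, enrol everyone aged 6 and over who participates, and stop when at least 7, 2 and 1 are reached. Each row rests on 8,000 simulated locations; the survey total is 2,800 times the unrounded mean per location.

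| Mean adults / 10-17 / 6-9 per household | Participation | Enrolled per location | Per cluster | Survey total | Exactly 7/2/1 |
|---|---|---|---|---|---|
| 3.0 / 0.857 / 0.429 | 100% | 18.2 | 72.8 | 50,946 | 2.9% |
| 3.0 / 0.857 / 0.429 | 70% | 17.5 | 70.1 | 49,044 | 3.7% |
| 2.5 / 0.714 / 0.357 | 100% | 17.6 | 70.4 | 49,286 | 4.0% |
| 2.5 / 0.714 / 0.357 | 70% | 17.2 | 68.9 | 48,244 | 4.6% |
| 3.5 / 1.0 / 0.5 | 100% | 18.4 | 73.6 | 51,525 | 2.5% |
| 3.5 / 1.0 / 0.5 | 70% | 17.8 | 71.3 | 49,881 | 3.3% |
| 3.0 / 0.6 / 0.3 | 100% | 21.5 | 85.9 | 60,144 | 2.7% |
| 3.0 / 0.6 / 0.3 | 70% | 21.2 | 84.6 | 59,230 | 3.5% |
| 3.0 / 1.0 / 0.6 | 100% | 16.6 | 66.5 | 46,571 | 3.2% |
| 3.0 / 1.0 / 0.6 | 70% | 16.2 | 64.7 | 45,280 | 3.5% |

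The first three mixes have the plan's 7:2:1 proportions. Across all rows the cluster holds 65-86 people instead of 40, the survey about 45,000-60,000 instead of 28,000, and the rules coincide in 2-5% of locations.

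**Age split when every member is enrolled.** In the first row the means per location are 12.78, 3.61 and 1.81 of 18.2, that is 70%, 20% and 10%. With a 7:2:1 population, enrolling everyone changes the number of participants but not the split.

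**Weights if the quota is kept.** Let M be the size measure used for cluster selection, N_g a cluster's population in age group g, and n_g the number enrolled (28, 8 or 4). Then the chance of selecting a cluster is about 10 x M_cluster / M_district, and the within-cluster weight is N_g / n_g. The product is M_district / (10 x M_cluster) x N_g / n_g. Since n_g is fixed, this is nearly constant within a district and age group wherever N_g / M_cluster is similar across clusters.

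**A weight to avoid.** One might weight by residents in visited households divided by number enrolled. That omits the fraction of the cluster visited. Take two areas of equal size with 2.8 adults and 0.8 aged 10-17 per household, but 0.2 versus 0.6 aged 6-9. More households must be visited to find a child in the first area, so the mean number of adults in visited households is 17.9 there and 11.2 in the second. The first area then gets 17.9 / (17.9 + 11.2) = about 62% of the adult weight instead of 50%.

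**The case against.** The strongest reply is that the sentence only marks eligibility: several members of one household may join until their age group is full. The later draw of one adult per household, for comparability, fits that reading. Alternatively the quota is a floor, as the minimum of 400 per district might suggest. Both readings are possible, so it would be too strong to say that the rules can never hold together. Neither is stated, however. The eligibility reading changes what the sentence says and still gives no way to choose among, say, four adults for one place. The floor reading breaks the fixed 40 per cluster and the planned 28,000.

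It is also fair that the 45,000-60,000 applies only to enrolling every member, which all the stated totals speak against.

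A reader might infer several stronger things that the documents do not support:

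- *The age split is lost or large households are under-represented whichever rule is followed.* Enrolling everyone keeps the population's split and takes every participating member of a large household. Under-representation is a risk only under the quota, and it is not quantified here.
- *The conflict makes availability a selection factor.* The inclusion criteria already require people to be available at the visit and willing.
- *Weights cannot be formed at all.* Clusters are drawn with probability proportional to size, and a fixed take is then roughly self-weighting within a district and age group. The weights are unspecified, not unobtainable.
- *No household counts will be recorded.* The Study procedures list none, but the ODK form is not in the documents.

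**Conclusion.** The concern stands as a conflict between stated rules together with a missing rule for the last places. The 28,000 and its split are exactly the quota, so the sentence on household members is the one out of line with the rest of the plan. The coincidence rate of about 2-5% and the 45,000-60,000 rest on assumed household distributions and participation of 70% or 100%. They show that the conflict would arise almost everywhere, and they do not forecast enrolment. Under the more plausible quota reading the consequence is discretionary choice of members and weights that the text does not define; the documents do not allow the resulting bias to be sized. This should be settled before fieldwork, because the selection step and household counts must be captured during the visits.

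**What to change.** - **Sampling method.** Replace the sentence with: *all members aged 6 years and older are eligible until the quota for their age group is filled.* Add that when eligible, consenting members outnumber the open places in an age group, the ODK form chooses among them at random.
- **Study procedures.** Record at each location the number of households visited and the eligible residents by age group.
- **Analysis plan.** Write out the weight: the inverse of the cluster selection probability, times cluster population in the age group divided by number enrolled in it, with the district-stage factor and the source of the population counts named. Do not use residents in visited households divided by enrolled unless it is also multiplied by the inverse of the fraction of the cluster visited.

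The cost is a change of wording, a short roster screen in ODK, a line in team training and slightly longer household visits. No extra participants are needed.

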#### **B] Health care workers**

We will select 100 healthcare workers from each of the 70 districts selected for the general population survey. We will conduct the survey for the HCWs in the district hospital and sub-district (taluk/CHC) levels. We will consecutively enrol the willing HCWs (Doctors, nurses, para medical staff and lab staff) working in the district hospital of the selected district. If we are unable to enrol 100 HCWs in the district hospital, then we will select sub-district (taluk/CHC) hospital for further enrollment till 100 HCWs are enrolled.

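### Sub-district health workers are eligible but are sampled only as overflow from the district hospital, so the pooled figure does not estimate national prevalence in the eligible population if prevalence differs by facility level

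*Combined protocol and SAP*

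**What the plan says.** Objective 2 reads "Estimate the prevalence of SARS-COV-2 antibodies among healthcare workers at the national level". Under Study population, B] Health care workers, the eligible group is doctors, nurses and paramedical or laboratory staff "employed at the district hospital and sub-district (taluk/CHC) levels, available at the time of hospital visit and willing to participate". Administrative and field staff are excluded.

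Sample size, B] gives the total: "We will enrol 7,000 health care workers across the country as done in the third survey". Sampling method, B] gives the allocation, "We will select 100 healthcare workers from each of the 70 districts selected for the general population survey", and the intended coverage, "We will conduct the survey for the HCWs in the district hospital and sub-district (taluk/CHC) levels". The operating rule comes next. It starts at one site: "We will consecutively enrol the willing HCWs (Doctors, nurses, para medical staff and lab staff) working in the district hospital of the selected district". It moves on only under a condition: "If we are unable to enrol 100 HCWs in the district hospital, then we will select sub-district (taluk/CHC) hospital for further enrollment". Enrolment stops once the district has 100.

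The section gives no staff list, no random selection of staff, no minimum or proportional share for sub-district workers, and no method for choosing the sub-district hospital. Analysis plan, B] is one sentence that promises a national prevalence with a 95% confidence interval. It mentions no weights, clustering or breakdown by facility level. Analysis plan, A] specifies both weights and clustering for the general population.

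**The concern.** The group defined as eligible and the group that can be sampled differ by rule. Eligibility and the coverage sentence put the two facility levels side by side, but the enrolment rule ranks them. A district with enough willing district-hospital staff contributes nobody from sub-district level. A district that falls short contributes a mix fixed by how many staff its hospital has and how many agree.

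The analysis then pools everyone into one national figure. If the two levels have the same prevalence, no harm is done. If they differ, the figure describes a facility mix that nobody chose. The confidence interval would not show this, because it reflects sampling error only. Weighting afterwards cannot repair a district in which one level had zero chance of selection.

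**Working it through.** **Inputs from the documents.** 70 districts and 100 workers per district (Sampling method, B]); total 7,000 (Sample size, B]); earlier health-worker seroprevalence of about 25% (introduction).

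**Inputs the documents do not give, assumed below.** The number of willing staff per district hospital (m), the sub-district share of eligible staff (w), the sub-district share of the sample (s), the prevalence difference between levels (d), and a design effect for health workers.

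**1. The plan's own figure.** 70 × 100 = 7,000, which reproduces. No precision target is stated for this sample, so no sample size formula can be checked.

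**2. What the rule does within a district.** The district-hospital share of the district's 100 is min(m, 100)/100.

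| Willing district-hospital staff, m | District-hospital share | Sub-district share |
|---|---|---|
| 25 | 25% | 75% |
| 50 | 50% | 50% |
| 51 | 51% | 49% |
| 75 | 75% | 25% |
| 100 or more | 100% | 0% |

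District-hospital staff are the majority once m exceeds 50. Sub-district staff have no chance of selection once m reaches 100.

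**3. Bias of the pooled figure.** Let P_D and P_S be the prevalences at district-hospital and sub-district level, and d = P_D − P_S. The sample estimates (1 − s)P_D + sP_S. The eligible population has (1 − w)P_D + wP_S. Subtracting, bias = (w − s) × d.

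| w | s | d (points) | Bias (points) |
|---|---|---|---|
| 0.3 | 0 | 5 | 0.3 × 5 = 1.5 |
| 0.7 | 0 | 15 | 0.7 × 15 = 10.5 |
| 0.8 | 0 | 10 | 0.8 × 10 = 8.0 |
| 0.5 | 0.25 | 5 | 0.25 × 5 = 1.25 |
| 0.4 | 0.25 | 5 | 0.15 × 5 = 0.75 |
| 0.4 | 0.5 | 10 | −0.1 × 10 = −1.0 |
| any | any | 0 | 0 |

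Rows with s = 0 assume no overflow in any district. Any overflow that brings s closer to w shrinks the bias. If s exceeds w, or if sub-district prevalence is the higher one, the sign changes.

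**4. Sampling error for comparison.** Half-width = 1.96 × √(deff × p(1 − p)/7,000). At deff = 2:

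- p = 0.25: 1.96 × √(0.375/7,000) = 1.43 points
- p = 0.50: 1.96 × √(0.500/7,000) = 1.66 points
- p = 0.80: 1.96 × √(0.320/7,000) = 1.33 points

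The full widths at p = 0.80 and p = 0.50 are 2 × 1.33 = 2.7 and 2 × 1.66 = 3.3 points. The design effect of 2 is borrowed from the calculation for children aged 6–9 under Sample size, A]. With 100 per district, deff = 1 + 99 × ICC, so deff = 2 implies an ICC of 1/99 ≈ 0.01. At an assumed ICC of 0.05, deff = 5.95 and the half-width is 2.5 points at p = 0.25 and 2.9 at p = 0.50.

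**The case against.** The strongest reply is that the selection rule is plain but its consequences are not measured. Most of that stands, and it limits what can be claimed.

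- **A reader might infer that the sample consists mainly of district-hospital staff.** The documents do not support this as a fact. They give no staff counts, and the plan itself foresees overflow. It is true in any district with more than 50 willing staff and would fail overall if most hospitals fell below that.
- **A reader might infer a bias larger than the whole confidence interval.** The 1.5–10.5 point range needs zero overflow in all 70 districts and a difference that no passage supplies. Its lower end, 1.5 points, is below the full width of 2.7–3.3 points. With a larger design effect the interval is wider still.
- **A reader might infer that the facility mix follows exposure.** The introduction places the occupational risk in hospital settings generally, and the taluk/CHC sites are called hospitals too. No passage ties hospital size or willingness to exposure. The only related figures show little gradient: about 25% in health workers against 24.1% in the general population in the third survey. Those figures pre-date the second wave and do not compare facility levels.
- **A reader might count missing field staff as bias.** They are an openly stated exclusion, so this is declared scope.

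It can also be said that national level only names the level of reporting, and that the design follows the third survey. Neither removes the mismatch. Eligibility names two facility levels, the rule can exclude one of them, and the analysis neither weights nor separates them. The documents carry over the third survey's total but do not say whether its selection rule was the same.

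**Conclusion.** The concern holds as a mismatch between the eligible population and the selection rule. It rests on the text alone: wherever the district hospital provides 100 willing workers, sub-district staff in that district have zero probability of selection, and nothing elsewhere in the plan corrects for it.

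The numerical consequence is conditional. The pooled figure misses the prevalence of the eligible population by (w − s) × d, which is zero if the levels do not differ or if the sample mix happens to match. Neither size nor direction can be fixed from the documents. The range of 1.5–10.5 points is a zero-overflow illustration with assumed w of 0.3–0.7 and d of 5–15 points. It shows only that a bias of the same order as the half-width of 1.3–1.7 points, or well above it, is possible.

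It would go too far to say that the health-worker survey has no usable result. It gives a usable estimate for a narrower group, provided that group is named.

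**What to change.** 1. Record the facility level (district hospital or sub-district) for every health worker enrolled.
2. Restate objective 2 and Analysis plan, B] so that the main estimate is for willing eligible staff of district hospitals in the 70 selected districts.
3. Report sub-district participants separately, with their own number and interval.
4. Do not present the pooled figure as the national prevalence for all eligible health workers.

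**Cost.** Fieldwork and site visits stay as planned. The claim is narrower, the report gains one table row, and the main estimate rests on somewhat fewer than 7,000 workers. For illustration, if three quarters of the sample came from district hospitals, n would be 0.75 × 7,000 = 5,250. The half-width at p = 0.50 and deff = 2 would then be 1.96 × √(0.5/5,250) = 1.9 points instead of 1.7.

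If an estimate for both levels is wanted, the alternative is to fix the split between levels in advance and weight by staff counts. That is a real trade-off. It needs staff counts that the documents do not show, and it adds sites, up to one more in each of the 70 districts, to a survey that allows two months including analysis. Staff at each site would still be consecutive volunteers.
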